#### Inclusion criteria

Gestational age between 30 0/7 and 36 6/7 weeks, and/or birth weight ≥ 1500 g.Age within 48 hours after birth.Use of a noninvasive ventilator for more than 30 minutes.Nasal continuous positive airway pressure (nCPAP), bi-level positive airway pressure (BiPAP), or non-invasive positive pressure ventilation (NIPPV) support ≥ 6 cmH_2_O, or high-flow nasal cannula (HFNC) support ≥ 6 L/min.Need for fraction of inspired oxygen (FiO_2_) ≥ 0.30 to maintain pulse oximetry oxygen saturation (SpO_2_) levels between 90 and 94%.Radiological evidence of RDS.

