### Outcomes {12}

#### Primary outcome measures

The SF index (SpO_2_/FiO_2_) at 1 day after PS administration.

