### Secondary outcome measures

The SF index before and after the administration of PS.The main monitoring time points are: before PS use and at 1 minute, 3 hours, 6 hours, and 12 hours after PS administration.Time taken for placement.Number of SpO_2_ fluctuations, episodes of bradycardia, and tachycardia during intubation.Whether PS could be aspirated from the stomach after administration.Administration of a second dose of PS due to NRDS (administered in the same manner as the first dose) (ethically assessed).Incidence of pneumothorax.

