## Assignment of interventions: allocation

### Allocation—sequence generation {16a} {16b}

After meticulous screening to ensure compliance with the inclusion criteria, eligible infants will be systematically randomized into one of two distinct groups: the LMA group or the INSURE group, adhering to a 1:1 allocation ratio. The randomization sequence will be computer-generated using R software (version 4.1.0, R Foundation for Statistical Computing, Vienna, Austria). To maintain allocation concealment, the randomization will be performed using sealed envelopes. Blocking will be used to enhance the balance and integrity of group assignments. In scenarios involving multiple births, each infant will undergo individual randomization to preserve the independence and validity of the study outcomes. This comprehensive approach underscores our commitment to methodological precision and the reliability of our clinical trial.

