## Statistical methods

### Statistical analysis {20a}

All analyses will be performed using SPSS software (IBM Corp., Armonk, NY, USA). Continuous variables will be summarized as means ± SD or medians (IQR), and categorical variables as *n* (%). The primary outcome, the SF index at 1 day after PS administration, will be evaluated for clinical equivalence between the LMA and INSURE groups using the TOST procedure based on an independent-samples t-test. Equivalence will be concluded if the entire 90% CI of the mean difference lies within the predefined margin of − 0.45 to + 0.45; if normality is not met, a nonparametric test will be applied. Secondary outcomes will be analyzed using t-tests or Mann–Whitney U tests for continuous variables and logistic regression or Fisher’s exact test for binary variables, as appropriate. If baseline imbalances are identified, multivariable linear or logistic regression will be performed to obtain adjusted estimates. A two-sided *P*-value < 0.05 will be considered statistically significant.

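### The primary equivalence test ignores the planned pre-surfactant SF index and adjusts only if imbalance is seen; one prespecified baseline-adjusted model would be more precise and leave no second estimate of undefined role

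*Protocol article*

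**What the plan says.** The Outcomes section of the protocol article defines the primary outcome as "The SF index (SpO_2_/FiO_2_) at 1 day after PS administration". Under Statistical analysis {20a}, it is tested for equivalence "using the TOST procedure based on an independent-samples t-test", with no covariate. The decision rule is: "Equivalence will be concluded if the entire 90% CI of the mean difference lies within the predefined margin", the margin being −0.45 to +0.45.

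After a sentence on the secondary outcomes, the same section adds: "If baseline imbalances are identified, multivariable linear or logistic regression will be performed to obtain adjusted estimates". It does not say how imbalance is to be judged, which covariates would enter, whether the sentence covers the primary outcome, or what standing the adjusted estimate has.

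The secondary outcomes schedule SF "before PS use and at 1 minute, 3 hours, 6 hours, and 12 hours after PS administration", so a baseline value of the primary variable is planned. Eligibility also rests on SpO2 and FiO2: "Need for fraction of inspired oxygen (FiO_2_) ≥ 0.30 to maintain pulse oximetry oxygen saturation (SpO_2_) levels between 90 and 94" per cent.

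On multiple births, Allocation {16a} {16b} states that "each infant will undergo individual randomization to preserve the independence and validity of the study outcomes".

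**The concern.** In a properly run randomised trial, any baseline difference between arms is due to chance. Seeing one is therefore a poor reason to change the model. The reason to adjust is that the covariate predicts the outcome, and this can be judged before any data are seen. A baseline value of the outcome itself is the obvious candidate.

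Two things are at stake. The first is precision: the unadjusted interval is wider than the planned data allow whenever baseline SF predicts day-1 SF. The second is clarity: in trials where imbalance is noticed, an adjusted interval will stand beside the unadjusted one. The equivalence conclusion is a yes or no, and the plan does not say what happens if the two disagree.

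A smaller point concerns multiples. Randomising siblings individually makes their allocations separate, but it does not make their outcomes independent, and the t-test treats them as independent.

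**Working it through.** **Inputs from the protocol (Sample size {14}).** Margin 0.45; mean 4.5 in both groups, so true difference 0; SDs 0.5 and 0.3; α = 0.05; power 90%; 23 per group required; 30 per group enrolled; 20% dropout. Pooled SD = √((0.25 + 0.09)/2) = 0.412. Evaluable infants per arm = 30 × 0.8 = 24.

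**Assumed.** The correlation r between baseline and day-1 SF, which is not in the document.

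**The plan's own figure.** Exact TOST power with SD 0.41 and true difference 0:
- At 0.025 per one-sided test, 22 per group gives 0.890 and 23 gives 0.907, so 23 is reproduced.
- At 0.05 per one-sided test, which is what the 90% CI implies, 19 per group is enough. Power is 0.957 at 23 and 0.964 at 24.

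**Half-width of the 90% CI.** Unadjusted: t(0.95; 46 df) × SD × √(2/24) = 1.679 × 0.412 × 0.2887 = 0.200. Adjusting for baseline SF multiplies this by about √(1 − r²). The loss of one degree of freedom changes it only in the fourth decimal.

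| Assumed r | Half-width | Equivalent sample, 1/(1 − r²) |
|---|---|---|
| 0 (unadjusted) | 0.200 | 1.00 |
| 0.2 | 0.196 | 1.04 |
| 0.3 | 0.191 | 1.10 |
| 0.5 | 0.173 | 1.33 |
| 0.6 | 0.160 | 1.56 |

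**Why r may be low.** Eligibility limits baseline SF to at most about 0.94/0.30 = 3.1. The expected day-1 mean of 4.5 lies close to the room-air ceiling of 1.00/0.21 = 4.76. Both restrict the range over which a correlation can show.

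**What the trigger recovers.** Simulation with 24 per arm, SD 0.41 and 40,000 runs per setting. Imbalance is assumed to mean P < 0.05 on baseline SF, since the protocol gives no criterion. The trigger then fires in about 5% of trials. Power at true difference 0:

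| Rule | r = 0.3 | r = 0.5 | r = 0.7 |
|---|---|---|---|
| Never adjust | 0.965 | 0.965 | 0.965 |
| Adjust only if imbalance is seen | 0.966 | 0.970 | 0.977 |
| Always adjust | 0.975 | 0.991 | 0.9995 |

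**Error rate.** Chance of wrongly concluding equivalence at a true difference of 0.45 (nominal 0.05):

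| Rule | r = 0.3 | r = 0.5 | r = 0.7 |
|---|---|---|---|
| Never adjust | 0.048 | 0.050 | 0.050 |
| Always adjust | 0.049 | 0.050 | 0.050 |
| Adjusted replaces unadjusted if imbalance is seen | 0.047 | 0.045 | 0.040 |
| Either may be claimed if imbalance is seen | 0.049 | 0.052 | 0.052 |
| Either may be claimed at any time | 0.060 | 0.071 | 0.080 |

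**If the SD is larger than planned.** With SD 0.6 and 24 per arm, power is 0.639 unadjusted, against 0.700 / 0.810 / 0.947 adjusted at r = 0.3 / 0.5 / 0.7.

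**Siblings.** For a given allocation, the t-test standard error is too large for pairs split across arms and too small for pairs in the same arm. Under individual 1:1 randomisation the two largely cancel. Simulating 48 infants with 25–50% in twin pairs, intraclass correlation 0.3–0.6, and block size 4 or one block of 48 (all assumed; 20,000 runs each) gave a t-test TOST error of 0.044–0.051 at a true difference of 0.45.

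**The case against.** The strongest reply is that the protocol does name a deciding analysis. The TOST sentence ties equivalence to the 90% CI from the t-test. The adjustment sentence comes later and never says that its estimates replace that interval. This stands. A reader might infer that the plan has no rule for which estimate decides, but the text does not support that. What is missing is only the role of the second estimate.

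A reader might also infer that the conditional rule inflates the error rate. The simulation does not show this for any rule that the text permits: error stays at about 0.04–0.05. It rises to 0.06–0.08 only if either interval could be claimed freely in every trial, which the protocol does not allow. How often the trigger would fire across several baseline variables cannot be stated, because neither their number nor the criterion is given.

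Third, the trial has power to spare: the half-width is 0.200 against a margin of 0.45. This also stands on the protocol's inputs, and r may be low. At r = 0.3 the gain in half-width is only 0.009.

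Fourth, covariate lists and imbalance criteria are often left to the analysis plan. That is fair for the details. It does not cover the trigger itself, which this document states.

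Finally, a reader might take the sibling remark to mean that the t-test is invalid. The simulated error rates do not support that.

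**Conclusion.** The point holds as an improvement in precision and prespecification. The protocol plans to measure the baseline value of its primary variable, leaves it out of the primary model, and brings it in only through a trigger that gains little and adds an estimate of undefined role.

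The gain is a half-width reduction from 0.200 to 0.191 / 0.173 / 0.160 at assumed r of 0.3 / 0.5 / 0.6, with 24 evaluable per arm and pooled SD 0.412. It shrinks towards nothing if r is low. With power already about 0.96 on the protocol's inputs, the trial is not underpowered for want of adjustment. The benefit would matter most if the SD proves larger than planned. The sibling issue is a loose claim in the allocation section with little net effect on the error rate.

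**What to change.** - Make the primary estimate the LMA minus INSURE difference in day-1 SF from one prespecified linear model with baseline SF and, if wished, gestational age. Judge its CI against the unchanged ±0.45 at the same 90% level, and state that this interval alone decides.
- Delete the imbalance trigger.
- Report the unadjusted t-test TOST as supportive.
- Reword the allocation section so that it does not imply independent outcomes for siblings. Add a sensitivity analysis that allows for sibling clustering, with a small-sample correction because only about 48 infants will be evaluable.

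The cost is one or two degrees of freedom and no additional infants. Baseline SF is already scheduled. The article does not mention a maternal or sibling identifier, so the sensitivity analysis needs a check that siblings can be linked. Under Protocol amendments {25}, a change to the analyses needs a formal amendment and ethics approval. Trial status gives an estimated end of recruitment of June 2026, so the amendment should be settled before outcome data are analysed.

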### Interim analyses {21b}

In alignment with the predefined statistical analysis plan, this trial does not include provisions for interim analyses of the outcomes. By adhering to this approach, the trial prioritizes the accuracy, reliability, and ethical integrity of its findings, ultimately contributing to the generation of high-quality evidence to inform clinical practice.

### Statistical methods—additional analyses {20b}

This trial did not involve other analyses such as subgroup analyses.

### Statistical methods—analysis population and missing data {20c}

The primary analysis will follow the intention-to-treat (ITT) principle. The ITT population will include all randomized participants, regardless of whether they received the allocated intervention, deviated from the study protocol, or withdrew from the study. Participants with missing data for the primary outcome will be handled using multiple imputation methods. A per-protocol (PP) analysis, which will include only participants who completed the study without major protocol violations, will be performed as a sensitivity analysis.

### Plans to give access to the full protocol, participant level-data and statistical code {31c}

Following the publication of primary endpoints, de-identified research datasets will be made available to qualified investigators upon formal request to the corresponding author, in compliance with institutional data-sharing agreements and applicable privacy regulations.

## Oversight and monitoring

### Composition of the coordinating center and trial steering committee {5d}

The coordinating center consists of a principal investigator, a data manager, and other research staff. The principal investigator oversees the experiment, providing overall direction, while the data manager is responsible for recording, organizing, and reviewing the data. Other research staff actively participate in the trial. Regular meetings will be held throughout the study to monitor progress, provide feedback on trial conditions, and convene emergency meetings if necessary. This study does not include a trial steering committee or stakeholder/public involvement group.

### Adverse events/side effects {22}

Throughout the trial, the safety of all enrolled infants will be closely monitored. Both expected and unexpected adverse events (AEs) will be systematically collected and coded using MedDRA. All AEs will be actively identified through routine clinical assessments and medical record reviews, and classified by the investigator according to severity, duration, and relationship to the study intervention. Serious adverse events (SAEs), including any suspected unexpected serious adverse reactions (SUSARs), will be documented and reported to the institutional ethics committee within 24 hours of awareness, following standard operating procedures. For publication consistency, only the incidence of predefined expected AEs (e.g., pneumothorax) will be reported.

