## Abstract

**Background:**

Neonatal respiratory distress syndrome (NRDS) is a life-threatening condition marked by progressive respiratory failure due to pulmonary surfactant (PS) deficiency, typically presenting within hours of birth. Exogenous pulmonary surfactant replacement therapy has significantly reduced mortality associated with NRDS and improved clinical outcomes. The current standard of care involves the intubation-surfactant-extubation (INSURE) technique. However, emerging evidence suggests that the laryngeal mask airway (LMA) may serve as a viable noninvasive alternative for neonatal resuscitation and therapeutic administration. This randomized controlled equivalence trial aims to compare the clinical efficacy and safety profiles of LMA and INSURE in delivering PS for NRDS management.

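### All adverse events are collected, coded and graded, but the protocol limits publication to the incidence of predefined expected ones, so the published harms comparison would be incomplete

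*Protocol article*

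**What the plan says.** The section Adverse events/side effects {22} of the protocol article sets a wide net for collection: "Both expected and unexpected adverse events (AEs) will be systematically collected and coded using MedDRA". It adds that "All AEs will be actively identified through routine clinical assessments and medical record reviews", and that the investigator classifies each event by how severe it was, how long it lasted and whether it was related to the intervention. Serious events, including suspected unexpected serious reactions, "will be documented and reported to the institutional ethics committee within 24 hours of awareness". The section then closes with a limit on what is published, justified by consistency of publication: "only the incidence of predefined expected AEs (e.g., pneumothorax) will be reported".

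The Background of the Abstract says that the trial "aims to compare the clinical efficacy and safety profiles of LMA and INSURE in delivering PS for NRDS management". The Dissemination section commits to journals, conferences and registries and says that publication will be unrestricted. The Data Availability section confines shared data to what the manuscript shows. The separate section on access to the full protocol, participant-level data and code offers de-identified datasets on request and sets no such limit.

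**The concern.** A reporting filter is written into the plan in advance. It cannot be put down to the article being a condensed version, or to an analysis plan that is not shown, because it is a positive rule and not a gap.

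The filter removes two things. The first is every event that is not on the predefined expected list. The second is everything except incidence for events that are on it, so the severity and relatedness grading done for each event would go unused in print.

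If equivalence on the SF index is shown, readers will weigh the laryngeal mask as an alternative to intubation, which is the purpose given under Objectives {7}. That judgement needs the full harms record from both arms. The article names one expected event as an example and does not show the list, so a reader cannot tell what has been excluded.

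**Working it through.** The plan states no figure on this point, so there is none to reproduce. The check is mainly a comparison of sections, followed by a small illustration.

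**Following an event through the plan**

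| Type of event | Collected, coded and graded | Sent to ethics committee | Published under the stated rule |
|---|---|---|---|
| Expected, not serious | Yes | Not stated | Incidence only |
| Expected, serious | Yes | Yes, within 24 hours | Incidence only |
| Unexpected, serious | Yes | Yes, within 24 hours | No |
| Unexpected, not serious | Yes | Not stated | No |

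The last two rows are the gap. An unexpected serious event has an oversight route but no publication route. An unexpected non-serious event has no stated outlet at all.

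**Does another section restore publication?**

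- *Abstract, Background:* the aim includes a comparison of safety profiles. A filtered list meets that aim only in part.
- *Dissemination {31a} {31c}:* publication is said to be unrestricted and results are to go to registries. It does not say that unexpected events will be included, and it is at odds with the filter.
- *Data Availability:* sharing stops at what the manuscript presents, so events left out of the paper are left out of the shared data too.
- *Plans to give access {31c}:* datasets are available on request without that limit. This conflicts with Data Availability, so a reader cannot rely on it.
- *Secondary outcome measures:* these include "Number of SpO_2_ fluctuations, episodes of bradycardia, and tachycardia during intubation", and also surfactant recovered from the stomach, a second dose, and pneumothorax. These will be compared whatever the adverse-event rule says.

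None of these sections expressly restores publication of unexpected events.

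**Illustration: would an unexpected harm be seen at all?**

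Inputs: n = 30 infants in the LMA arm, from Sample size {14}. The true event rate p is an assumption, because the documents give none; a range is shown.

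Formula: P(at least one event) = 1 − (1 − p)^30.

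- p = 1%: 1 − 0.99^30 = 0.260, or 26%
- p = 2%: 1 − 0.98^30 = 0.455, or 45%
- p = 5%: 1 − 0.95^30 = 0.785, or 79%
- p = 10%: 1 − 0.90^30 = 0.958, or 96%

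A rare unexpected harm would more likely than not go unseen in a trial of this size. A moderately common one would probably be recorded, and the rule would then keep it out of the paper. The figures give only the chance of seeing one event; they do not measure how far a conclusion would be distorted, and a single event in a preterm infant need not be caused by the device.

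**The case against.** The best defence is that the foreseeable harms of the procedure are already prespecified as secondary outcomes, with tests given under Statistical analysis {20a}. Serious events reach the ethics committee, independent auditors look at participant safety, and the primary equivalence test is untouched. The promise of unrestricted publication may also mean only that nobody can veto a paper, which would soften that particular contradiction. All of this is fair, and it narrows the point. It does not answer it: the prespecified outcomes are the anticipated harms, ethics reporting and audit are oversight and not publication, and the conflict with the safety aim remains.

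A reader might infer several stronger things that the documents do not support:

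- *That harms are concealed altogether.* Serious events do reach the ethics committee. The omission is from the published results.
- *That all serious events go unreported.* One on the expected list would still count towards the published incidence.
- *That harms of the laryngeal mask are the ones most likely to be missed.* The expected list is not shown, and the Background cites earlier clinical studies of this route, so known mask-related harms could be on it.
- *That the rule tilts the result towards the laryngeal mask, or towards no difference in harm.* It applies to both arms and would equally suppress unexpected harms of intubation.

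**Conclusion.** The point stands as a reporting rule that is wrong as written. Under it, the publication would omit unexpected adverse events in both arms, serious or not, and the severity and relatedness of all events. The harms comparison would be incomplete, with the direction of any bias unknown. Collection of data and the primary analysis are not affected.

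This conclusion rests on the text alone and needs no figure. The 26% to 96% range holds only for the assumed rates of 1% to 10% and 30 infants in the arm. It shows that the rule could matter in practice, not that it will.

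**What to change.** Delete the closing sentence of Adverse events/side effects {22}. In its place, commit to reporting all adverse events and all serious adverse events, expected and unexpected, by arm: number of infants affected, number of events, severity and relatedness. State whether the arm is as randomised or as treated; either can be defended for harms if it is named in advance.

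Reconcile four sections so that they say the same thing: Adverse events/side effects {22}, Dissemination {31a} {31c}, Plans to give access {31c}, and Data Availability. In particular, settle whether shared data stop at what the manuscript shows.

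The cost is one table from data already collected and coded, and an amendment by the route in Protocol amendments {25}. No change to sample size, data collection or the primary analysis is needed.

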### Frequency and plans for auditing trial conduct {23}

Audits will be conducted periodically throughout the study to ensure compliance with the protocol, regulatory requirements, and ethical standards. The frequency of audits will be determined based on study milestones. Independent auditors will oversee the trial’s conduct, focusing on data integrity, participant safety, and protocol adherence. Audit findings will be reported to the principal investigator as needed.

